### Procedures

At baseline, respondents will be asked about their winter sport demographic characteristics, winter sport skill level, physical fitness, current injuries and physical complaints, winter sport preparation, and winter sport injury preventive measures. Furthermore, skiers and snowboarders in the intervention and control group will be asked to report the injury preventive measures they usually take during their preparation for their winter sport holiday. One month and three months after baseline, skiers and snowboarders will be asked to report retrospectively in detail what they had done up until then regarding injury prevention during their current winter sport preparation and holiday. In the follow-up measurements, respondents will be asked about any injuries they suffered during their winter sport preparation and holidays. In our study, an injury is defined as an event during skiing or snowboarding after which the participants have to stop their winter sport activities or are unable to participate in another winter sport activity [12-15]).

For all three measurements, an online form will be sent by email by 1 researcher through SurveyMonkey, an online questionnaire system (www.surveymonkey.nl). The first reminder will be sent after 1 week if no response is received. A second reminder will be sent after 2 weeks if no response is received.

The intervention group will be additionally questioned about their use and valuation of the Wintersportklaar intervention. The evaluation of its effectiveness will not take place in an experimental setting; participants in the intervention group will be given access to the intervention, but no further conditions are applied to the use of the intervention. In the questionnaires given at one month and three months, the intervention group will be asked about their use of the intervention, the appeal of the intervention, the behavioral actions they took after being exposed to the intervention, their intention to use the intervention again, and how they would want to be informed about the intervention. If participants indicate that they do not want to use the intervention, they will be asked to explain their decision in detail.

### Statistical Analysis

Descriptive analyses (mean, standard deviation, frequency, range) are conducted for the different baseline variables for both study groups. To evaluate the success of the randomization, baseline values are analyzed for differences between the intervention and control groups (chi square, independent *T* tests and/or Mann-Whitney test).

Chi square tests and/or logistic regression analyses will be used to analyze behavioral change according to the intention to treat principle. According to this principle all participants who were enrolled and randomly allocated to the intervention or control group are included in the analysis and are analyzed in the groups to which they were randomized. In a secondary analysis, behavioral change is analyzed according to the non-intention to treat principle. The proportion of injured winter sport participants is calculated by dividing the number of injured respondents by the total number of respondents in this study and per study group. Differences in the proportion of winter sport injury between the intervention and control groups are assessed using logistic regression analysis (significance level set at *p*<.05).

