### Sample Size and Allocation

In this study, the assumption is made that a 10% increase in favorable injury preventive behavior in the intervention group compared with the control group can be achieved. To achieve 80% power with a significance level of 0.05, and taking into account a potential loss to follow-up among participants of 10% over the winter sport season, the sample size calculation reveals that 423 skiers and snowboarders per study group are needed in this study. Eligible participants will simultaneously be allocated at random to the intervention or control group after T0, using a computerized random number generator (the ASELECT function in Excel). No restrictions will be imposed for the allocation; simple randomization will be performed. All steps in the randomization process will be done by 1 researcher.

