### Injury Preventive Behavior

In our study, our main outcomes measure injury preventive behavior defined as: (i) taking winter sport lessons; (ii) performing strength exercises; (iii) the use of protective equipment; and (iv) knowledge of the 10 FIS rules for the conduct of safety in winter sport. Each injury preventive topic is divided into preparatory acts like searching for information about injury preventive measures, buying a winter sport helmet, etc, and structural injury preventive measures (eg, wearing a helmet, taking lessons). Taking winter sport lessons consists of two preparatory acts and three structural injury preventive measures. Performing strength exercises consists of two structural injury preventive measures, and the use of protective gear consists of three preparatory acts and three structural injury preventive measures. Finally, knowledge of the 10 FIS rules for the conduct of safety in winter sport consists of three preparatory acts. All injury preventive behaviors are assessed through single questions (eg, Did you buy a winter sport helmet after the start of this study? Yes/No/Not applicable).

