Another challenge is the use of injury preventive behavior and/or a change in injury preventive behavior as a primary outcome measure in a study regarding injury prevention rather than winter sport injuries. Clear definitions of injury preventive behavior are necessary, as well as extensive measurements of injury preventive behavior at baseline and subsequent measurements. Furthermore, we have to determine what a relevant change in injury preventive behavior is. In this study, we limit injury preventive behavior to taking winter sport lessons, performing strength exercises, the use of protective equipment, and knowledge of the 10 FIS rules of conduct. To enhance the measurement of injury preventive behavior, each injury preventive behavior topic will be operationalized in preparatory acts and structural injury preventive measures. To better detect change in our measurements, we use dichotomous answer categories instead of, for example, a 5-point scale. Finally, it is well-known that changing health-related behavior is difficult [16]. It is a lengthy process that requires small steps. Therefore, a relevant change in injury preventive behavior was set at 10%, which we think is an achievable change.

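### The plan allows an unadjusted chi-square test as the only main analysis despite baseline behavior, skill and fitness data, and uses significance tests to judge randomization

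*Protocol article*

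**What the plan says.** For the main outcome, the Statistical Analysis section says: "Chi square tests and/or logistic regression analyses will be used to analyze behavioral change according to the intention to treat principle". It gives no rule for choosing and names no covariates. In the same paragraph the injury comparison is given a single method, logistic regression at the 5% level.

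On baseline data the section says: "To evaluate the success of the randomization, baseline values are analyzed for differences between the intervention and control groups". The tests listed are chi-square, t and Mann-Whitney. Under Sample Size and Allocation, allocation follows T0 and is simple randomization from a computerized random number generator, without restrictions.

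Under Procedures, the T0 questionnaire covers skill level, physical fitness, preparation and preventive measures, and "skiers and snowboarders in the intervention and control group will be asked to report the injury preventive measures they usually take". Follow-up at one and three months asks what was done in the current preparation and holiday. The example item under Injury Preventive Behavior is "Did you buy a winter sport helmet after the start of this study", answered yes, no or not applicable.

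The hypothesis and the sample size are framed as a difference between arms: "a 10% increase in favorable injury preventive behavior in the intervention group compared with the control group can be achieved". The Discussion describes the primary outcome as "the use of injury preventive behavior and/or a change in injury preventive behavior as a primary outcome measure".

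**The concern.** Three things are fixed badly.

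- **The main test is open.** A chi-square test of arm against a follow-up item cannot use the T0 answers, and the text permits it as the only analysis. A person's usual habit is a natural predictor of what that person does this season. Simple randomization does not balance that habit by design, so using it in the analysis can only be expected to help precision. Leaving both methods open also lets the choice be made after results are seen.
- **Baseline tests are given a job they cannot do.** If the generator was used as described, every baseline difference is due to chance, and a small p-value says nothing about whether randomization succeeded.
- **The target is worded as change.** The hypothesis and the sample size concern a difference between arms at follow-up. T0 asks about usual practice and follow-up about the current season, so subtracting one from the other would not give a clean within-person change.

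At stake are some precision, a main result that depends on an unstated choice of method, and a baseline table that invites wrong conclusions about the randomization.

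**Working it through.** **Inputs.** From Sample Size and Allocation: "To achieve 80% power with a significance level of 0.05"; a 10% increase, read here as 10 percentage points; 10% loss to follow-up; 423 per group. The article gives no control proportion and no sidedness. I assume 40% or 50% in the control group and a two-sided test. The correlation ρ between T0 and follow-up behavior is not in the article either, so it is varied.

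**1. The plan's own figure.** Unpooled two-proportion formula, 50% versus 60%:

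n = (1.960 + 0.842)² × (0.50×0.50 + 0.60×0.40) / 0.10² = 7.849 × 0.49 / 0.01 = 384.6

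384.6 × 1.1 = 423.1, which matches 423. A comparison of 40% versus 50% gives the same result. One-sided versions give at most 365 per arm and do not fit. The sample size is therefore consistent with an unadjusted two-sided comparison.

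**2. Power of the unadjusted test.** Analysed per arm: 423 × 0.9 = 380.7, about 381. For 50% versus 60%:

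- Null SE = √(2 × 0.55 × 0.45 / 381) = 0.0360
- Alternative SE = √(0.49 / 381) = 0.0359
- Power = Φ[(0.10 − 1.960 × 0.0360) / 0.0359] = Φ(0.82) = 79%

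This is essentially the planned 80%. For 20% versus 30% it is 89%.

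**3. Power with adjustment for T0 behavior.** To a linear approximation, adjustment multiplies the residual variance by 1 − ρ², so the effective n is 381 / (1 − ρ²). The last two columns are a simulation with 40,000 runs, comparing the chi-square test with a test stratified on a binary baseline behavior.

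| Assumed ρ | Effective n per arm | Approximate power, 50% vs 60% | Simulated, unadjusted | Simulated, stratified |
|---|---|---|---|---|
| 0 | 381 | 79% | 79.8% | 79.2% |
| 0.2 | 397 | 81% | 80.2% | 81.1% |
| 0.3 | 419 | 83% | 80.0% | 83.1% |
| 0.5 | 508 | 89% | 80.2% | 89.4% |
| 0.7 | 747 | 97% | 80.1% | 97.6% |

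For 20% versus 30%, 89% rises to 92% at ρ = 0.3 and 96% at ρ = 0.5.

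**4. Baseline tests.** With sound randomization and k independent tests at 0.05, P(at least one p<.05) = 1 − 0.95^k. This is 23% for k = 5, 40% for k = 10 and 64% for k = 20. Baseline variables are correlated in practice, so these figures are a guide.

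**5. How far adjustment can reach.** The article's item counts are: lessons 2 preparatory and 3 structural; strength exercises 2 structural; protective gear 3 and 3; FIS rules 3 preparatory. That makes 16 items, of which 2 + 3 + 3 = 8 are preparatory acts. An act dated from the start of the study, such as buying a helmet, may have no matching T0 item. For such items the ρ in the table need not apply, and T0 skill and fitness may be the only usable covariates.

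**The case against.** The strongest reply is that the article excludes nothing. Logistic regression can carry T0 behavior, and a covariate list is often left to a fuller document. That stands: a reader might infer that baseline behavior is left out of the analysis, but the text does not say so. The point is narrower: the article allows a test that cannot adjust to be the only one.

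A reader might also infer that power is wasted or the trial underpowered. The figures do not support this. The unadjusted test gives about the planned power, and any gain depends on a correlation the article does not report.

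Nor do the documents support the reading that the effect cannot be estimated. The between-group difference at follow-up is estimable and is what the hypothesis states. No section sets out a T0-to-follow-up subtraction, and the item dated from study start is one example, not a description of the whole follow-up questionnaire. The looseness is in the word change.

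The article does not say that baseline p-values will select covariates, so that harm is only possible. Chance imbalance is not bias; the test's error rate already covers it. Without covariates, chi-square and logistic regression would give nearly the same p-value at this size. The open choice therefore matters mainly if covariates enter later.

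Finally, the Results section says analysis is under way, so adding covariates now carries its own risk of post hoc choice. This stands, and the fix has to deal with it.

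**Conclusion.** The concern holds as an improvement available at almost no cost, not as a flaw that invalidates the trial. The article leaves the main analysis open to an unadjusted chi-square although useful T0 data exist in both arms, and it prescribes baseline tests that cannot show whether randomization worked.

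The forgone gain is about 2 percentage points of power at ρ = 0.2, 4 at 0.3 and 10 at 0.5, and nothing at 0. This rests on an assumed 50% versus 60%, 381 analysed per arm, and a T0 item that matches the outcome. At a lower control rate the unadjusted power is already higher and the gain smaller. The finding on baseline tests needs none of these assumptions; only the 23% to 64% illustration assumes independent tests.

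**What to change.** 1. Name one primary analysis: logistic regression of each follow-up behavior on arm, adjusted for the matching T0 behavior where one exists and for T0 skill level and physical fitness as collected. Standardize the result to a between-group risk difference with 95% CI.
2. Describe the target throughout as the difference between arms at follow-up, in line with the Objective and Hypothesis and Sample Size and Allocation sections, instead of behavioral change.
3. Keep the unadjusted chi-square test as a supportive analysis.
4. Present the baseline table descriptively, without significance tests.
5. Fix the covariates before any comparison by arm. If comparisons have already been made, report when and on what basis the covariates were chosen.

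Covariates should be limited to what T0 is documented to contain. Procedures does not name ski versus snowboard as a T0 item. The four fitness and skill classes come from the intervention's own questionnaire, which the control group does not receive, so they cannot be used.

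The cost is a change of wording and slightly more analysis work. No new data are needed.

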## Introduction

Skiing and snowboarding are very popular winter sports worldwide, including among Dutch residents. Nearly one million Dutch snow sport fanatics travel each year to the mountains to spend their winter holidays in the snow, with Austria, France, Germany, Switzerland, and Italy being the most popular destinations [1]. Besides the beneficial health effects of being active, both skiing and snowboarding are also associated with a risk for musculoskeletal injuries and traumatic brain injury (42 injuries per 1,000,000 person-years for skiers and 19 injuries for snowboarders in America or 0.6 injuries per 1,000 skier days in Austria) [2-4]. Although the injury rate among skiers in Austria has decreased in recent years, attention to injury prevention should be encouraged due to the severity of these injuries [2,4].

Known risk factors for the occurrence of snow sport injuries are snow sport experience, rented equipment, weather conditions, speed, fatigue and technical errors [5,6]. The development of safer skiing environments and the use of injury preventive measures—especially a winter sport helmet—might prevent or reduce injury severity among skiers and snowboarders. However, because injury preventive measures such as helmet use for adults and wrist guard use for snowboarders in general are not compulsory on the ski slopes, a behavioral change in skiers and snowboarders is necessary to increase the use of those measures and subsequently prevent or reduce injuries in winter sports.

Accordingly, a scientific research project has started in the Netherlands (funded by ZonMW, the Netherlands Organization for Health Research and Development). The aims of this project are: (i) to develop an evidence-based intervention to stimulate injury preventive behavior among skiers and snowboarders; and (ii) to evaluate the effectiveness of the developed intervention. The effectiveness of the developed intervention will be evaluated through a randomized controlled trial. This article describes the design of this study.

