## Discussion

This article describes the design of a study that will evaluate the effectiveness of an intervention on injury preventive behavior in skiers and snowboarders. A major challenge of this study is related to the recruitment of participants and their adherence to this study. A total of 848 skiers and snowboarders will enroll for this study. To recruit respondents, several strategies are used (eg, social media such as Facebook, LinkedIn, and Twitter, and the possibility to preregister for the study). In a previous study, we also used social media to recruit skiers and snowboarders. Within two weeks, we received 300 responses, without the use of any rewards for participants or paid advertisements on social media. For this study, respondents will be offered a chance to win a money prize if they complete all three questionnaires. The chance to win a reward (€250) is used to enhance the willingness of skiers and snowboarders to participate in the study and the respondents’ adherence to the study, even after their winter sport holidays are over. In combination with the possibility to preregister for the study and the use of paid advertisements on (eg, Facebook), we believe that the recruitment of 848 skiers and snowboarders will be challenging, but feasible.

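### Injury is compared by an unqualified logistic regression at p<.05 although event counts may be too low for it, and the injury definition does not match the injury question

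*Protocol article*

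**What the plan says.** The Statistical Analysis section of the protocol article defines the proportion injured by "dividing the number of injured respondents by the total number of respondents in this study and per study group". It then fixes the test: "Differences in the proportion of winter sport injury between the intervention and control groups are assessed using logistic regression analysis", at a significance level of p<.05. It names no small-sample form of the model and does not call the comparison exploratory. No expected number of injuries and no power for injury are given anywhere; Sample Size and Allocation concerns injury preventive behavior only.

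The Introduction quotes two background injury rates: "0.6 injuries per 1,000 skier days in Austria" and "42 injuries per 1,000,000 person-years for skiers and 19 injuries for snowboarders in America". Neither is applied to the trial.

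Procedures contains two adjacent statements on injury. At follow-up, "respondents will be asked about any injuries they suffered during their winter sport preparation and holidays". But "an injury is defined as an event during skiing or snowboarding after which the participants have to stop their winter sport activities"; being kept from a further such activity by the event also qualifies. Strength exercises are among the advice given to the intervention group, which can also sign up for a weekly personal exercise schedule (Intervention).

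**The concern.** A method and a threshold are fixed for an outcome that may yield only a handful of events. With so few, maximum-likelihood logistic regression can fail to give a finite odds ratio, and its p-value can depend heavily on which test the software reports. A result above .05 would say little about injury, yet nothing in the article warns the reader of that.

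The second issue is what counts as an injury. A strain from strength training at home is within the question put to participants but outside the stated definition. One arm is advised to do such exercises, so this part of the injury picture could drop out of the comparison between arms.

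**Working it through.** **The plan's own figure.** The only sample size stated is that "423 skiers and snowboarders per study group are needed in this study", for a 10% increase in behavior, 80% power, alpha 0.05 and 10% loss. The control proportion is not given. For a two-sided test without continuity correction, 35% v 45% needs 376 per arm, and 376/0.9 = 418. For 40% v 50% it is 388, and 388/0.9 = 432. So 423 is reproducible to within 3% with a control proportion near 35% to 40%, and it does not bear on injury.

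**Inputs for injury.**
- Rate: 0.0006 per skier day (Introduction, Austria).
- Respondents: 423 × 0.9 = 381 per arm, 762 in total (Sample Size and Allocation). The Discussion gives 848 enrolled against 2 × 423 = 846, which makes no difference here.
- Ski days per participant: **not stated**. Assumed 6, range 5 to 14.
- The American person-year rates are not used: 846 × 42/1,000,000 = 0.036 injuries in a full year, which would make the case more extreme.

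**Expected injuries, both arms, no effect** = 762 × days × 0.0006.

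| Assumed days | Risk per person | Expected injuries |
|---|---|---|
| 5 | 0.0030 | 2.3 |
| 6 | 0.0036 | 2.7 |
| 10 | 0.0060 | 4.6 |
| 14 | 0.0084 | 6.4 |

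**Chance of an empty arm.** At 6 days, one given arm has no injury with probability (1 − 0.0036)^381 = 0.253. At least one arm is empty with probability 1 − (1 − 0.253)² = 0.44. With 423 per arm and no loss it is 0.39. At 14 days, (1 − 0.0084)^381 = 0.040, and 1 − (1 − 0.040)² = 0.08. With an empty arm, the ordinary logistic odds ratio is zero or infinite.

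**What the p-value does then.** Take three injuries split 0 v 3, with 381 per arm. Fisher's exact test gives p = 0.25. The likelihood-ratio statistic from ordinary logistic regression is about 2 × 3 × ln 2 = 4.16, above the 3.84 cut-off for p = .05. The Wald test is uninformative because its standard error diverges. Yet with three injuries and no effect, all three fall in one arm with probability of about 2 × (1/2)³ = 0.25. By Fisher's test, 0 v 5 gives 0.062, and 0 v 6 (p = 0.031) is the first all-in-one-arm split below .05.

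**Exact (Fisher) power for a halved risk, 381 per arm.**
- At the quoted rate: 0.15% at 6 days and 2.7% at 14 days.
- At 5 times the rate (0.0036 × 5 = 0.018): 11%. Expected injuries are 762 × 0.018 = 13.7 with no effect, or 381 × 0.018 × 1.5 = 10.3 under a halving.
- At 10 times (0.036): 27%. Expected injuries are 27.4 with no effect, or 20.6 under a halving.
- With 423 per arm and no loss, the last two powers are 12% and 30% exact, or 20% and 36% by normal approximation.

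At 5 times the rate, an empty control arm has probability (1 − 0.018)^381 = 0.001, so the lack of a finite estimate largely disappears. Low power does not.

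**Definition against question.** An injury on snow before the holiday, for example in a lesson, is asked about and meets the definition. An injury off snow during preparation, for example from strength exercises, is asked about and does not meet it.

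**The case against.** **The event count is not the protocol's.** A reader might infer that the quoted rate implies about three injuries in the trial. The article does not support that. It never gives ski days, never applies the Austrian rate to its participants, and does not say how those injuries were defined. Participants are inexperienced or of low fitness, the Introduction lists experience as a risk factor, and injuries are self-reported, so the true rate may well be higher. This stands: the count is conditional, and the estimability problem largely goes away at 5 to 10 times the rate.

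**Injury is not primary.** The objective, hypothesis, sample size and main outcomes all concern behavior, and the Discussion says so openly. Low power for such an outcome is not itself an error. This also stands. What remains is that a significance test is fixed without qualification.

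**The choice of model could be left to an analysis plan.** It could have been, but here the article names both the model and the threshold.

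**The denominator.** Some respondents may not have skied by the last form, so it is tempting to count only those who have been on holiday. That would select on an event after randomization. The article's denominator keeps the randomized comparison and should stay.

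**Preparation injuries.** A reader might infer that all of them are excluded, or that reports are collected and discarded. On-snow events still count, and the article does not say what happens to the other reports. Nor does it support calling exercise injury the only plausible harm. Only the mismatch between the two statements is established.

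**Conclusion.** The point holds in a limited form. The injury comparison is fixed as an unqualified logistic regression test at p<.05. If the Austrian rate applied, it would rest on about 2 to 6 injuries over an assumed 5 to 14 ski days, with a 44% chance at 6 days (8% at 14) of an arm with none. At 5 to 10 times that rate (also an assumption) the model can usually be fitted, but exact power for a halving is about 11% to 27%. Across this whole range, a non-significant result could not be read as absence of an effect on injury. The primary behavior analysis and its sample size are unaffected.

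The inconsistency in Procedures needs no assumption: off-snow preparation injuries are within the question and outside the definition.

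**What to change.** In the analysis and the report:

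1. Keep all respondents, by randomized arm, as the denominator.
2. Report injury counts and proportions by arm with an exact 95% confidence interval for the difference or ratio. If a model is wanted, use Firth logistic regression.
3. Label the comparison exploratory and state that a non-significant result is not evidence of no effect on injury.
4. Reconcile the injury question with the injury definition in Procedures, and report off-snow preparation injuries (for example from strength exercises) as a separate row by arm.

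The article says enrolment is complete and analysis under way. None of this needs new data, since preparation injuries are already asked about. The cost is some wording, one extra table and a less definitive statement on injury.
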